## Discussion

First, this study will expand public health knowledge about breast cancer surveillance practices among YBCS, their perceived facilitators and barriers to screening, and their willingness to advocate for their high-risk female relatives. Special attention will be given to minority YBCS. The study will allow us to further understand the needs of these high-risk women including barriers to breast cancer screening. Due to random sample selection and random allocation, study findings can be generalized to all YBCS and high-risk relatives in the state of Michigan and possibly to other U.S. states with similar demographic composition and similar availability and accessibility of breast cancer screening services. Second, confirmation of family history will occur simultaneously with identification of the YBCS in the cancer registry followed by outreach to her high-risk female relatives. By circumventing the typical barriers associated with family history collection (i.e., client awareness of family history, provider practices regarding family history collection and referral), the study aims to increase breast cancer screening among women at greatest risk for breast cancer. This innovative approach of identifying high-risk women through existing public health data may lead to a new method of family history collection and breast cancer risk assessment. Third, this study is among the first to evaluate two versions (Targeted vs. Enhanced Tailored) of a printed intervention as a means of increasing breast cancer screening in YBCS and their high-risk female relatives. This novel approach will likely expand our knowledge about interventions that can increase breast cancer screening among women at substantially higher risk.

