### Setting

The Michigan Cancer Surveillance Program is a central cancer registry that was established by law (Act 82 of 1984) [9] to collect reports on cases for *in situ* and invasive malignancies. Between 1998 and 2007, there were 7,866 YBCSs identified in the Michigan Cancer Surveillance Program [10]. This database will be used to identify and recruit YBCS. The Michigan Department of Community Health-Genomics Program and the University of Michigan-School of Nursing will enroll participating families, implement the two versions of the intervention, and collect and analyze baseline (Time 1) and follow up (Time 2) data.

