### Recruitment of YBCS and high-risk relatives

Between 1994 and 2008 there were 9,000 cases of young women with breast cancer were reported to the Michigan Cancer Registry. For the study, 3,000 women diagnosed with invasive or in –situ-breast cancer between 20 to 45 years old from 1994 to 2008 will be randomly selected from the cancer registry database. The Michigan Cancer Surveillance Program will cross-reference mortality data to exclude deceased YBCS. To increase inclusion of minority and underserved women, the sample will be stratified by race. The study will oversample YBCS who are black and living in counties with the highest mortality rates for young women with breast cancer (See Figure 1).

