**Figure 1 F1:**
[figure not shown]
Age-adjusted ten-year mortality rates for breast cancer by county among women in Michigan under age 50, 2000–2009.

As shown in Figure 2, it is estimated that from the initial 3,000 YBCS, approximately 1,200 will be willing to participate (40% response rate). We estimate that approximately 20% of these YBCS (n = 240) will not have any eligible high-risk female relatives (e.g. relatives will be younger than 25 or older than 64). These YBCS will be included in the study but will be analyzed as a separate group. Based on our previous experience recruiting women with familial breast cancer and their high-risk relatives [11], we project that the remaining 960 YBCS will have approximately 1,728 eligible high-risk female relatives. This estimation is based on the assumption that we will be able to identify 1.8 first- and/or second-degree, high-risk relatives per YBCS. Based on our previous experience [11], we expect that 604 high-risk relatives will be willing to participate in the study (35% response rate). Table 1 describes inclusion and exclusion criteria for YBCS and high-risk female relatives.

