### Statistical analyses

Analyses will be conducted separately for YBCS and high-risk relatives. A descriptive analysis of baseline data will provide screening utilization practices, perceived barriers and facilitators to screening, and other outcomes for YBCS and high-risk relatives. This will include tabulating counts and frequencies of variables including demographics, cancer history, screening history and perceived breast cancer risk. Bivariate analyses (using the Chi-square test for differences in proportions and *T*-test for differences in means) to assess the associations between demographic factors, clinical indications and screening practices will follow. We will stratify by using the Cochran-Mantel-Haenszel test to assess the association between family history, screening practices, genetic counseling/testing, and perceived facilitators/barriers while controlling separately for race/ethnicity, age-group, and time since diagnosis. Outcomes include both continuous and dichotomous measures. Means and standard deviations will be used to describe the results. Continuous measures taken only at post-test will be compared between the two intervention groups by simple t-tests. After assuming an autocorrelation of data r = .30, changes over time in continuous measures will be tested by paired t-tests. For dichotomous measures taken only at post-test, the rates in the two groups will be compared by logistic regression. The proportions in each group will be reported to describe the results. If a baseline version of the measure is available, logistic regression will be conducted on the post-tests with the pre-tests included as covariates. Chi-square tests will be conducted to test the changes over time. The above analyses will establish whether the groups are equivalent, determine whether post-tests differ between the two groups, and assess the significance of changes over time. To further meet Aim 3, regression analyses (linear or logistic) will be used to test which factors (beyond the intervention) predict obtaining breast cancer screening.

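### The stated generalisation to all Michigan survivors and high-risk relatives does not follow from a disproportionate survivor sample with 40% expected response and a non-random sample of relatives

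*Protocol article*

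**What the plan says.** **The claim.** The Discussion states: "Due to random sample selection and random allocation, study findings can be generalized to all YBCS and high-risk relatives in the state of Michigan". It gives two grounds, how the sample is selected and how women are allocated to arms.

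**Survivors.** Under Recruitment of YBCS and high-risk relatives, 3,000 women "will be randomly selected from the cancer registry database". In the same paragraph, "the sample will be stratified by race", and "The study will oversample YBCS who are black and living in counties with the highest mortality rates for young women with breast cancer". No sampling fractions or stratum sizes are given. Of the 3,000, 1,200 (40%) are expected to take part. A reporting facility or physician may ask that a woman not be contacted (recruitment step 2).

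**Relatives.** Genetic counselors identify up to two per survivor, and an alternate may replace a non-responder (recruitment step 6). Table 1 requires US residence, not Michigan residence, and a survivor willing to make contact. Response is put at 35%, or 604 of 1,728.

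**Analysis.** For the baseline description, the Statistical analyses section says: "This will include tabulating counts and frequencies of variables including demographics, cancer history, screening history and perceived breast cancer risk". Race/ethnicity, age group and time since diagnosis enter one at a time as controls in Cochran-Mantel-Haenszel tests of association. Weights are neither mentioned nor ruled out.

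**Registry size.** Setting: "Between 1998 and 2007, there were 7,866 YBCSs identified in the Michigan Cancer Surveillance Program". Recruitment: "Between 1994 and 2008 there were 9,000 cases of young women with breast cancer".

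**The concern.** Random selection lets a plain sample percentage stand for the population only if selection probabilities are equal, or their inequality is undone in the analysis, and if response is near complete or unrelated to the outcome. Here the probabilities are unequal by design and most selected women are expected not to respond. Random allocation makes the two arms comparable; it says nothing about whom the enrolled women represent. For relatives there is no random selection to appeal to.

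At stake is how the descriptive results on screening use may be read. If an overall survivor percentage is reported as Michigan's, part of it may reflect the oversampling and who replied. If a relatives' percentage is reported as Michigan's, it describes a population that was not sampled.

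**Working it through.** **1. The article's own flow.** 3,000 × 0.40 = 1,200 survivors. 960 × 1.8 = 1,728 eligible relatives. 1,728 × 0.35 = 604.8, stated as 604. All reproduce. Survivor non-response is 1 − 0.40 = 0.60. For relatives the two response rates multiply to 0.40 × 0.35 = 0.14. The article states no precision target for Aims 1 and 2.

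**2. Grounds against design.**

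| Group | Random selection | Random allocation |
|---|---|---|
| Survivors | Random but disproportionate by race and county; 60% expected not to respond | Supports the arm comparison only |
| Relatives | None: counselor-chosen, survivor must be willing to contact, any US residence, 35% response | Supports the arm comparison only |

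**3. Oversampling (survivors).** If no weights are used and response is equal across strata, bias = (s − W) × d. W is the population share of the oversampled stratum, s its sample share, and d the difference in screening between that stratum and the rest. The cost of design weights is the Kish design effect, W²/s + (1 − W)²/(1 − s). The article gives none of W, s or d. Assumed ranges: W 10–20%, s 25–50%, d 0–20 points.

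| W | s | d = 0 | d = 10 | d = 20 | Design effect |
|---|---|---|---|---|---|
| 10% | 25% | 0 | 1.5 | 3.0 | 1.12 |
| 10% | 50% | 0 | 4.0 | 8.0 | 1.64 |
| 15% | 25% | 0 | 1.0 | 2.0 | 1.05 |
| 15% | 40% | 0 | 2.5 | 5.0 | 1.26 |
| 20% | 25% | 0 | 0.5 | 1.0 | 1.01 |
| 20% | 50% | 0 | 3.0 | 6.0 | 1.36 |

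Bias is in percentage points. The largest is (0.50 − 0.10) × 20 = 8 points; the smallest is 0.

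**4. Non-response (survivors).** Bias = (1 − response rate) × (responder rate − non-responder rate). With 0.60 and assumed differences of 0, 5, 10 and 20 points, this is 0, 3, 6 and 12 points. With no assumption at all, a proportion p among responders leaves the proportion among all selected women between 0.40p and 0.40p + 0.60, a band 60 points wide. Design weights alone do not touch this bias. It may add to the oversampling bias or offset it.

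**5. Scale.** At p = 0.5 and n = 1,200, the 95% half-width under simple random sampling is 1.96 × √(0.25/1,200) = 2.8 points. The biases above run from nothing to several times that.

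**6. Registry counts.** 7,866/10 = 787 cases per year for 1998–2007. The other five years of 1994–2008 are left with 9,000 − 7,866 = 1,134, or 1,134/5 = 227 per year. A constant rate would give 786.6 × 15 = 11,799.

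**The case against.** The strongest reply is that this is a condensed article. Weighting of descriptive tables is the kind of detail it leaves to a full protocol or analysis plan, which is not shown. That stands. A reader might infer that the tables will be unweighted and that the Aim 1 and 2 estimates are therefore biased. The article supports neither step: it is silent on weights, and bias needs screening to differ by oversampled stratum or by response status, for which no rates are given. Zero lies within every range above.

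A reader might also infer that confidence intervals would miss the state value too often. No interval for an Aim 1 percentage is planned in the article, so that does not follow either.

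Three further replies stand. Aim 1 as worded is to survey 3,000 survivors and determine their screening status; the claim to represent all Michigan women comes from one Discussion sentence. Estimates within race are less affected by the oversampling, though its county component remains. The internal validity of the Aim 3 arm comparison is untouched.

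On the registry counts, 9,000 exceeds 7,866, so the totals do not contradict each other outright. Nor are they what weights would use: those need stratum counts when the sample is drawn, after deceased women are removed.

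None of this rescues the sentence itself. It is a positive claim that names its own grounds, and weighting is not among them. No unseen weighting scheme could turn the relatives into a random sample of Michigan relatives.

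**Conclusion.** The point holds in this form: generalisation to all Michigan survivors and relatives does not follow from the design. For relatives it fails outright, since they are neither randomly selected nor confined to the state. For survivors it would need design weights and a non-response adjustment, and would still rest on an assumption about unmeasured causes of response. Random allocation is no ground for it.

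Whether overall survivor percentages would be biased, how much and in which direction, cannot be determined from the article. The figures of 0 to 8 points (oversampling) and 0 to 12 points (non-response) rest wholly on assumed shares and differences, and show only that the effect could be negligible or could exceed the sampling error. The two registry counts imply very different yearly rates, and rounding would not plausibly close the gap; this is a separate matter for clarification.

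**What to change.** - **Overall Aim 1 survivor estimates presented as statewide:** apply design weights, the registry's stratum count at sampling divided by the number selected in that race-by-county stratum. Add a non-response adjustment from registry variables for all 3,000 selected women, such as race, county, age and year of diagnosis, and in situ or invasive disease. State that this does not remove bias from unmeasured causes of response.
- **Discussion sentence:** restrict the claim to those weighted survivor estimates, delete random allocation as a ground, and drop the claim for relatives, limiting inference to the women enrolled.
- **Aim 3:** leave the arm comparisons unweighted.
- **Registry counts:** say what the 7,866 and the 9,000 each count and why their implied yearly rates differ.

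Cost: text edits and some registry programming. The registry withholds identifiable data until consent, so it would have to compute the adjustment itself or supply de-identified stratum data; the article does not say whether it would. Intervals widen by the square root of the design effect. That is about 3% to 12% for a 15% population share and a 25–40% sample share (√1.05 to √1.26), and 1% to 28% over the whole assumed range (√1.013 to √1.64), before any further loss from the non-response adjustment.

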## Abbreviations

YBCS: Young breast cancer survivor; DCIS: Ductal carcinoma in situ; CA: Cancer.
